## Introduction

Knee osteoarthritis (KOA) ranks highly among global causes of disability and chronic pain, particularly in people over 50 years of age [1]. Structured exercise programs, dietary weight management, and mind-body exercise (such as tai chi and yoga) were considered by the panel to be effective and safe for all patients with knee OA [2–5]. These updated OARSI guidelines recommended non-pharmacological as the core treatments for KOA in all cases [6].

Massage is a safe and non-pharmacological treatment with limited contraindications and no known serious adverse events [7]. Traditional Chinese massage has a positive effect on KOA and widely used in China. In recent several studies have shown that Chinese massage therapy decreased pain and may improve extensor muscle strength, and it may improve walking ability for these KOA patients; however, different massage sects in China caused assessment difficulties for the treatment of KOA [8, 9]. In order to standardize massage techniques and procedures, we organized multi-disciplinary experts in China to conduct a questionnaire survey and field discussions and successfully acquire an evidence-based traditional Chinese medicine massage treatment of knee osteoarthritis [10].

Topically administered non-steroidal anti-inflammatory drugs (NSAIDs) such as Diclofenac solution attained significantly greater improvement in pain reduction in patients with KOA and are widely used in the world [11–14]. However, local skin reactions happened more commonly in patients treated with topical NSAIDs [15].

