### Study setting and recruitment

The study will be carried out at the five hospitals: Guang’anmen Hospital, Beijing’s Capital Medical University Traditional Chinese Medicine Hospital, Dongfang Hospital of Beijing University of Chinese Medicine, Xuan Wu TCM Hospital Beijing, and Beijing Fengsheng Trauma-Orthopedic Hospital of Traditional Chinese Medicine. The study will recruit participants with KOA who meet the diagnostic criteria of the American College of Rheumatology through hospital outpatient [16]. WeChat official account is one of the Chinese popular social media platforms of Guang’anmen Hospital and brochures. Meanwhile, the recruitment of participants has started in June 2018.

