### Interventions

#### Experimental group

Two hundred patients in the experimental group will receive 20 sessions of manual massage treatment (2 sessions weekly for 10 weeks,10 min one session). Use the definite evidence-based traditional Chinese medicine massage technique for knee osteoarthritis to do the massage treatment [10].

During the treatment period, other Chinese and Western drugs and treatment methods (including physical therapy and psychotherapy, etc.) for knee osteoarthritis are not used. In cases of intolerable knee pain, the patients will be instructed to take loxoprofen sodium tablets (60 mg, oral 3/day) as a rescue medication. The use of other treatments, such as injections of any kind, moxibustion, acupuncture, or cupping, will not be allowed.

When combined with other diseases, the drugs and treatments must be continued, and the drugs and treatments need to be recorded in detail in the combined medication list.

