#### Control group

One hundred patients in the control group will receive External Diclofenac Diethylamine Emulgel (Beijing Novartis Pharma Ltd. producing, trade name: Vitalin Emulgel) treatment (3–4 times per day for 10 weeks). Other interventions will be similar to the experimental group.

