### Statistical analysis

All statistical analyses will be performed with the SPSS software (SPSS 20.0, SPSS Inc., Chicago, IL, USA) by statisticians who are independent of the research team and blinded to the group allocation. Data analysis will be based on the intention-to-treat (ITT) principles. All numerical data will be presented as the mean ± SD, and categorical variables will be described with percentages (%). All the statistical tests are bilateral inspection; *p* < 0.05 is considered statistically significant. Paired *t* test or the paired rank sum test is used for the comparison within the groups; the *χ*^2^ test or Fisher’s exact probability method is used for the count data, and the Wilcoxon rank sum test is used for the rank data between groups. CMH *χ*^2^ test is used for the primary outcome of WOMAC improve rate. It is necessary to adjust the baseline and centers of the changes in WOMAC score between the groups with the covariance method.

The secondary outcome includes CSKO score, X-ray data, and MRI data, which are all measurement data, and a group *t*-test or the Wilcoxon rank-sum test is used for comparison between the groups. The *χ*^2^ test or Fisher’s exact probability method is used for participants’ dropout and adverse events rate analysis.

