## Discussion

Massage treatments through pressing, pinching, flexion-extension, stretching, plucking, rubbing, and other bone-setting manipulations are all recommended. According to traditional Chinese medicine (TCM), massage on the epidermis of the body can stimulate and adjust the distribution of meridians, qi, and blood. According to modern medicine, massage may improve systemic immune and inflammatory profiles in healthy individuals [24]. As a supplementary and alternative therapy, massage has been widely used in clinical practice and was widely recommended by Chinese orthopedic experts.

Although some studies shown effectiveness and safety for all patients with KOA treatment by traditional Chinese massage or Diclofenac solution, however, as far as we know, our study will be the first randomized controlled and multicenter clinical trial. In this study, evidence-based traditional Chinese medicine massage treatment VS External Diclofenac Diethylamine Emulgel will be conducted in participants with KOA to observe the correlation between clinical manifestations and changes in X-ray and MRI, so as to further understand and identify the effectiveness and safety of both treatment methods.

In order to avoid the bias of results and improve the reliability of clinical results, we try to keep the baseline consistency as much as possible. Participants will be screened strictly according to the inclusion and exclusion criteria. All the researchers will be trained to understand the design of the study. To achieve blindness in the course of the intervention, the sealed envelopes should be attached to massage and External Diclofenac Diethylamine Emulgel before the intervention. In order to maintain the consistency of massage techniques, all Chinese massage therapists involved in the study have achieved strict massage training. In the study, MRI images of the affected limb were taken for MRI score of cartilage defects in both groups. All participants will be carried out in the above five hospitals. This study also has several limitations. First of all, Chinese massage therapists and participants in the waiting list will not be blinded due to the nature of the intervention. Secondly, the long-term efficacy of massage therapy will not be observed due to the observation treatment period of the study is only 10 weeks.

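### The named WOMAC analyses make no allowance for therapist clustering in the massage arm; if the therapist ICC is above zero, precision is overstated, by an amount the article does not let one fix

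*Protocol article*

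**What the plan says.** In the protocol article, Statistical analysis, two analyses of the primary outcome are named. For WOMAC change: "It is necessary to adjust the baseline and centers of the changes in WOMAC score between the groups with the covariance method". For the responder version, a CMH chi-square "test is used for the primary outcome of WOMAC improve rate". On sidedness, "All the statistical tests are bilateral inspection", with significance at p < 0.05. The section mentions no therapist term, random effect or cluster-robust error, and no confidence interval. The Introduction, however, states a non-inferiority hypothesis.

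On delivery, the Experimental group section gives each of 200 patients 20 hands-on sessions over 10 weeks. Under Control group, "One hundred patients in the control group will receive External Diclofenac Diethylamine Emulgel", with no therapist involved. "The study will be carried out at the five hospitals" that are then listed (Study setting and recruitment). There is more than one therapist: "all Chinese massage therapists involved in the study have achieved strict massage training" (Discussion). Their number, their caseload, and whether a patient keeps the same therapist throughout are not stated.

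**The concern.** When a treatment is delivered by hand, patients of one therapist tend to share whatever that therapist does better or worse than colleagues. Here this can happen in the massage arm only, a partially nested design. Ordinary covariance analysis and the CMH test both take patients as independent, given the terms they adjust for. If therapists differ, the massage mean is less certain than those methods report.

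Variation between therapists is plausible. The Introduction motivates the trial by saying that "different massage sects in China caused assessment difficulties for the treatment of KOA", and standardising the technique is the response to that. The Blinding section also says that therapists know the allocation, so therapists could differ in manner as well as in technique.

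At stake is the validity of the standard error and of the p < 0.05 rule. The same holds for whatever interval is eventually set against a non-inferiority margin. The error has one direction: a positive ICC makes the stated tests anti-conservative.

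**Working it through.** **The plan's own figure.** The Sample size section gives a minimum of n = 85.49 per group from effective rates of 95.6% and 79.8%. The usual two-proportion superiority formula with unpooled variance is

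n = (z_α + z_β)² × [p1(1−p1) + p2(1−p2)] / (p1−p2)².

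Alpha is two-sided 5%. Power is not stated and is inferred as 90%, for which the rounded constant (z_α + z_β)² is 10.5:

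n = 10.5 × (0.956×0.044 + 0.798×0.202) / 0.158² = 10.5 × 0.20326 / 0.024964 = 85.49.

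The figure reproduces. It is a calculation for independent patients, with no design effect.

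**Inputs for the clustering check.** From the article: 200 massage and 100 gel patients, five centres, two-sided 5%. Assumed, because the article gives neither: the ICC, and the number of therapists (hence m patients per therapist, with m = 200 / number of therapists). Equal caseloads and one therapist per patient are also assumed.

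**Formulas.**
- Design effect in the massage arm: DE = 1 + (m − 1) × ICC.
- Variance ratio of the difference, true to reported: (DE/200 + 1/100) / (1/200 + 1/100).
- SE ratio: the square root of the variance ratio.
- Actual type I error: 2 × [1 − Φ(1.96 / SE ratio)].

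**Low end (20 therapists, m = 10, ICC 0.02).** DE = 1 + 9×0.02 = 1.18. Variance ratio = (0.0059 + 0.01)/0.015 = 1.06. SE ratio = 1.03. Type I error = 5.7%.

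**High end (10 therapists, m = 20, ICC 0.05).** DE = 1 + 19×0.05 = 1.95. Variance ratio = (0.00975 + 0.01)/0.015 = 1.317. SE ratio = 1.147. Type I error = 8.8%.

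**Does centre adjustment remove it?** A centre main effect shifts both arms equally. A therapist effect shifts massage patients only, so it behaves like a treatment-by-centre or treatment-by-therapist interaction, which the named model does not contain. This holds even with one therapist per hospital. It was checked by simulating the covariance analysis with baseline and five fixed centre effects, 10,000 runs per scenario. Entries are true SE / reported SE, with the type I error of the nominal 5% test:

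| Therapists (m) | ICC 0.02 | ICC 0.05 | ICC 0.10 |
|---|---|---|---|
| 5 (40) | 1.13, 8.3% | 1.31, 13.3% | 1.53, 19.7% |
| 10 (20) | 1.08, 6.9% | 1.16, 9.4% | 1.30, 13.2% |
| 20 (10) | 1.03, 5.5% | 1.09, 7.4% | 1.16, 8.9% |
| 40 (5) | 1.01, 5.3% | 1.03, 5.6% | 1.06, 6.3% |

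At ICC 0 the ratio was 1.00 and the error 5%. The simulation agrees with the formula to within a few hundredths in the SE ratio, and centre adjustment does not cure the problem.

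**Effect on power.** At the planning rates with 200 and 100 patients (unpooled), power is about 96% at ICC 0 and about 87% in the worst case tabulated (5 therapists, ICC 0.10).

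**The case against.** The strongest reply is that the article condenses a full protocol which the Data Availability section says exists, and that an analysis plan may exist too. Random-effect structure is commonly left to such documents, and naming baseline and centre does not exclude a therapist term. This stands as a caution: therapist effects may be handled elsewhere. But the article does not merely stay silent on the model. It names the adjustment terms, and those terms do not match how the treatment is delivered.

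Second, a reader might infer that massage outcomes are clustered and that the interval is too narrow as a matter of fact. The documents do not support that. They give no ICC, therapist number, caseload or continuity of therapist, and the section names no confidence interval. The remark on massage sects describes prior practice. The trial answers it with a standardised technique and common training, both of which should reduce therapist variance. They do not show it to be zero.

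Third, a simple nested effect fits only if each patient has one main therapist. Over 20 sessions therapists may rotate; the clustering would then probably be weaker and its structure different. This stands and shapes the fix.

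Fourth, inference restricted to these trained therapists is a defensible target, under which their differences are not sampling error. That is why a sensitivity analysis is an acceptable minimum. The article, however, offers the treatment to clinicians generally and does not limit its claim to these therapists.

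**Conclusion.** The point holds in conditional form. Both named analyses of WOMAC lack any allowance for therapist, the clustering can arise in the massage arm only, and centre adjustment does not remove it. If the ICC is positive, the standard error and p-value, and any interval used for non-inferiority, overstate precision.

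The size cannot be fixed from the article. Assuming 10 to 20 therapists, equal caseloads, one therapist per patient and an ICC of 0.02 to 0.05, the formula puts the true SE about 3% to 15% above the reported one and the type I error at about 5.7% to 8.8%. With 40 therapists and ICC 0.02 the effect is negligible; with very few therapists and a high ICC it is material.

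A reader might also infer that the trial is too small. It is not shown to be: power at the planning rates stays at about 87% or more throughout the range examined. The issue is the validity of the test, not the sample size.

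**What to change.** - Record the main treating therapist of each massage patient. The Trial status section predicts completion of recruitment by September 2021 and the article is dated July 2022. If that prediction held, the identifier would have to be recovered from treatment records, and the article does not say whether these hold it.
- Analyse WOMAC change with a partially nested linear mixed model: baseline and centre as fixed effects, a random therapist effect in the massage arm only, and small-sample (for example Satterthwaite) degrees of freedom. SPSS MIXED is a suitable procedure. Report the therapist variance. The minimum is to pre-specify this model as a sensitivity analysis to the covariance analysis.
- Add a matching therapist-adjusted check of the responder analysis, since a linear model leaves the CMH test unchanged.
- If patients were shared among therapists, use the main therapist or a multiple-membership structure, and state which.
- If the full protocol or analysis plan already handles therapist, say so and align the article's wording.

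The cost is one identifier per massage patient, possibly retrospective, and one model term. Intervals become slightly wider, and if therapists are few their variance will be poorly estimated. If that variance proves near zero, little precision is lost.

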**Methods and design:**

A randomized controlled trial in which 300 participants diagnosed with KOA will be recruited and randomly allocated to either the experimental group or the control group in a ratio of 2:1. Two hundred participants will receive evidence-based traditional Chinese medicine massage 2 sessions per week for 10 weeks as the experimental group, and 100 participants will receive External Diclofenac Diethylamine Emulgel 3–4 times per day for 10 weeks as the control group. The patients in the two groups will receive follow-up at two time points at 5 weeks and 10 weeks from the beginning of treatment, respectively. The MRI scans and X-ray will be performed at baseline and at the end of the intervention. The primary outcome will be the changes in the Western Ontario and McMaster Osteoarthritis Index (WOMAC). Secondary outcomes will be measured by the PRO scale for knee osteoarthritis based on the concept of traditional Chinese medicine (Chinese scale for knee osteoarthritis (CSKO)), X-ray evaluation, and MRI scan evaluation. The data of WOMAC and CSKO will be analyzed at the baseline, 5 weeks, and 10 weeks from the beginning of treatment. The data from MRI scans and X-rays will be analyzed at baseline and at the end of the intervention. The significance level sets as 5%. The safety of interventions will be evaluated after each treatment session.

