### Randomization

In this study, this clinical research adopts randomized blocks, and cases will be randomly assigned to each center. The results of the random groups will be placed in sealed envelopes, which are numbered consecutively. When the patients are enrolled, they take the envelopes in the order of enrollment and will be grouped according to the contents of the envelopes. In the waiting list group, in a ratio of 2:1, there are 200 cases in the experimental group and 100 cases in the control group. The random sequence will be generated by an independent professional statistician who is not involved in the study with the SPSS software (SPSS 20.0, SPSS Inc., Chicago, IL, USA). The random numbers will be stored by a fixed non-involved person.

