### Sample size

According to the literature, the average effective rate of treating knee osteoarthritis only through massage is 95.6% and 79.8% by application of external diclofenac diethylamine emulsion latex [15]. According to the sample size calculation formula, the minimum sample size of each group is *n* = 85.49. Considering expulsion case and getting significant results, at the same time, in order to implement layered research in the experimental group, we planned the ratio of the cases in the experimental group and the control group is 2:1, and the number of included cases was 300. There were 200 cases in the experimental group, and 100 cases were in the control group.

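### With 2:1 allocation, the covariance analysis of WOMAC change should use a standard error that does not assume equal spread in the two arms

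*Protocol article*

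**What the plan says.** The protocol article makes change in WOMAC the primary outcome (Abstract; Outcomes). Its Statistical analysis section attaches two analyses to WOMAC:

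- For the change in score: "It is necessary to adjust the baseline and centers of the changes in WOMAC score between the groups with the covariance method".
- For the proportion improved, a CMH chi-squared "test is used for the primary outcome of WOMAC improve rate".

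Allocation is 2:1. The Randomization section states that "there are 200 cases in the experimental group and 100 cases in the control group", and the Sample size section repeats these numbers. The level is 5% (Abstract) and "All the statistical tests are bilateral inspection". The secondary measurements (CSKO, X-ray, MRI) are compared between groups by a t test or the Wilcoxon rank-sum test.

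The article does not say how the standard error of the adjusted difference is to be obtained. It gives no standard deviation of WOMAC, or of its change, for either arm.

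**The concern.** Analysis of covariance, taken plainly, estimates one residual variance from both arms together. That estimate is weighted by arm size, so about two thirds of it comes from the 200 massage patients. The variance of the treatment difference is weighted the other way: with equal spread, the 100 gel patients contribute (1/100)/(1/200 + 1/100) = two thirds of it. At 1:1 the two weightings agree and unequal spread cancels. At 2:1 they do not.

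If gel patients vary more than massage patients, the interval is too narrow and the test rejects too often. If massage patients vary more, the interval is too wide and power is lost. A larger trial does not cure this, because the bias depends on the allocation ratio and not on the total number. The Introduction states a non-inferiority hypothesis. If that is judged by a confidence interval from this model, the interval carries the same bias.

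**Working it through.** **Inputs from the article:** 200 massage and 100 gel patients (Randomization; Sample size), two-sided 5% (Abstract; Statistical analysis), adjustment for baseline and centre (Statistical analysis), five hospitals (Study setting and recruitment). **Assumed:** the gel/massage ratio r of residual SDs, because the article gives none.

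**The plan's own figure.** The Sample size section gives 85.49 per group from response rates of 95.6% and 79.8%. With unpooled variances:

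n = (z_a + z_b)² × [p1(1−p1) + p2(1−p2)] / (p1−p2)² = 10.5 × (0.042064 + 0.161196) / 0.158² = 10.5 × 0.20326 / 0.024964 = 85.49

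The constant 10.5 is the rounded value for two-sided 5% and 90% power; the article does not state the power. The figure reproduces, but it concerns a responder proportion and says nothing about the SD of WOMAC change.

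**Standard error at 200:100.** Set the massage residual SD to 1 and the gel SD to r.

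- Variance used by the model: [(199 + 99r²)/298] × (1/200 + 1/100)
- True variance: 1/200 + r²/100
- SE ratio k = square root of (model / true)
- Actual size = 2 × [1 − Φ(1.96k)]

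Example, r = 1.25 (r² = 1.5625): model (199 + 154.69)/298 × 0.015 = 0.01780; true 0.005 + 0.015625 = 0.02063; k = 0.929; size 6.9%.

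The last two columns come from simulated trials with no treatment effect, analysed with arm, baseline and five centres (normal residuals, 20,000 runs per ratio; Monte Carlo standard error near 5% is √(0.05 × 0.95/20,000) = 0.15 percentage points).

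| r (gel/massage) | Model variance | True variance | k | Size, formula | Size, simulated | Size with HC3, simulated |
|---|---|---|---|---|---|---|
| 0.67 | 0.01225 | 0.00949 | 1.136 | 2.6% | 2.5% | 4.6% |
| 0.8 | 0.01321 | 0.01140 | 1.076 | 3.5% | 3.6% | 4.9% |
| 1 | 0.01500 | 0.01500 | 1.000 | 5.0% | 4.9% | 4.7% |
| 1.25 | 0.01780 | 0.02063 | 0.929 | 6.9% | 6.8% | 4.9% |
| 1.5 | 0.02123 | 0.02750 | 0.879 | 8.5% | 8.5% | 4.8% |

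**Same total at 150:150.** Model variance is [(149 + 149r²)/298] × (2/150) = (1 + r²)/150, which equals the true variance for every r. Simulated size was 4.8% to 5.2%.

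**Sample size does not help.** For large numbers at 2:1, k² tends to (2 + r²)/(1 + 2r²). At r = 1.5 this is 4.25/5.5 = 0.773, so k = 0.879, the same as in the table.

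**The case against.** The best case against is that the article states no fault. It names a covariance method without a variance estimator, and that choice is commonly left to a full protocol or SAP, which may already specify a robust one. Ordinary analysis of covariance with 2:1 allocation is also common and accepted. This stands in part: nothing in the article is misstated, and the point is a recommendation. It remains worth making because the plain reading of the method, joined to the stated allocation, leaves the error rate dependent on an assumption that need not be made.

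Three stronger readings are tempting, and the documents do not support them.

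- **That the planning rates show unequal spread.** The Sample size section says "the average effective rate of treating knee osteoarthritis only through massage is 95.6% and 79.8% by application of external diclofenac diethylamine emulsion latex". The responder variances p(1−p), 0.042 and 0.161, follow mechanically from the rates and say nothing about the SD of WOMAC change. Two normal distributions with the same SD, cut at one threshold, give exactly these rates if their means differ by 1.706 − 0.834 = 0.87 SD.
- **That the direction is known.** One could argue that percentage reductions cannot exceed 100%, so the better-responding massage arm would bunch at the limit and gel would vary more. That depends wholly on an assumed distribution. Normal reductions capped at 100% and matched to the planning rates give SD ratios from 1.00 (underlying SD 15 points) to 1.42 (40 points), and the article gives no SD with which to choose. It also concerns percentage reduction, not the change in score. Therapist delivery could equally widen the massage arm.
- **That the whole primary conclusion is at risk.** The CMH test of the improvement rate is also attached to the primary outcome and uses no pooled residual variance. The article does not say that the covariance analysis alone decides the trial.

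**Conclusion.** The point holds as a conditional risk and a free improvement. If the covariance analysis is run in its ordinary form and the residual SDs differ, 2:1 allocation makes its standard error wrong. The size is modest for mild differences (3.5% to 6.9% for SD ratios 0.8 to 1.25), larger at 0.67 to 1.5 (2.6% to 8.5%), and nil when spreads are equal. Neither the existence nor the direction of a difference can be read from the article.

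The conclusion rests on two assumptions: that the covariance method means a single residual variance, and the chosen range of SD ratios. It covers the analysis of WOMAC change, and by the same argument any equal-variance t test on the secondary outcomes. It does not touch the CMH test or the sample size figure.

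**What to change.** Keep the model for WOMAC change with arm, baseline WOMAC and centre. Add one sentence to the analysis plan: the standard error, confidence interval and p value for the arm effect will come from a heteroscedasticity-consistent (HC3) estimator, or from a model with a separate residual variance in each arm. Name one of the two. State that any between-group t test kept for CSKO, X-ray or MRI data will be in the unequal-variance (Welch) form.

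Fix this before the allocation is revealed, since choosing the estimator after seeing the spreads would be data-driven. Confirm that the named software (SPSS 20.0) can produce the chosen estimator, or name a program that can.

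The cost is the added wording, with no new data or patients. If spreads turn out equal, little is lost: HC3 size at r = 1 was 4.7% against 4.9% for the ordinary form, and in a further 5,000 simulated trials with equal spread the average HC3 standard error was about 1.3% larger.

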### Outcomes

The efficacy between the two groups will be assessed by primary outcome measure: change in WOMAC score three times (week 0, week 5, week10) (Fig. 1). The secondary outcomes measured at three time points (week 0, week 5, week10) included the Chinese Scale for Knee Osteoarthritis (CSKO), and at two points (week 0, week10) included *X-ray and MRI*.

In order to observe the time to effect, we measure the primary and secondary outcomes at week 5 and week 10, respectively; however, only the clinical results of week 10 were used as the final evaluation outcomes.

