### X-ray data acquisition

Taking X-ray of the double knee joint with weight loading is at the adem position. The Kellgren and Lawrence classification criteria will be used on AP film to evaluate the degree of degeneration and the width of medial and lateral tibiofemoral joint space [17]. At the end of treatment, the X-ray of the double knee joint was taken again. Compare the width changes of medial and lateral tibiofemoral joint space on standard load positive X-ray before and after treatment.

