### MRI data acquisition

Using Siemens 3.0T MRI to obtain the patient’s knee T2 mapping sequence. Using the Recht criteria to evaluate cartilage degeneration [23]. Measure the average thickness and volume of cartilage at the same time.

After the end of treatment, MRI images were taken of the affected limb for the MRI score of cartilage defect.

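### Continuous secondary outcomes are compared without the baseline and centre adjustment planned for WOMAC, and ordered imaging grades are classed as measurements: valid, but precision is lost

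*Protocol article*

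**What the plan says.** All references are to the protocol article.

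- **Statistical analysis, secondary outcomes.** "The secondary outcome includes CSKO score, X-ray data, and MRI data, which are all measurement data". The sentence goes on to offer a group t-test "or the Wilcoxon rank-sum test is used for comparison between the groups". No covariate is named, and no rule chooses between the two tests.
- **Statistical analysis, WOMAC.** "It is necessary to adjust the baseline and centers of the changes in WOMAC score between the groups with the covariance method".
- **Statistical analysis, general rule.** "the Wilcoxon rank sum test is used for the rank data between groups".
- **X-ray data acquisition.** "The Kellgren and Lawrence classification criteria will be used on AP film", and joint-space width is measured medially and laterally. The before-after comparison named there is the change in width.
- **MRI data acquisition.** "Using the Recht criteria to evaluate cartilage degeneration"; cartilage thickness and volume are measured too. The post-treatment scan is said to serve an MRI score of cartilage defect, and the Discussion repeats this for both groups.
- **Outcomes; Methods and design.** CSKO is taken at weeks 0, 5 and 10, and imaging at baseline and end of treatment. Week 10 is the final evaluation.
- **Study setting; Randomization.** There are five hospitals, with block randomisation that appears to run within centre, 200 patients against 100.

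**The concern.** Two things in one short paragraph do not fit the rest of the article.

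First, the article recognises that baseline and centre belong in the model for the WOMAC change. It then names methods for CSKO, joint-space width, cartilage thickness and cartilage volume that use neither, and gives no reason. Each of these has a baseline value. Leaving it out keeps explainable variation in the error term and leaves chance baseline imbalance in the estimate. The result is wider intervals and lower power on the outcomes meant to show whether imaging and the Chinese scale agree with WOMAC.

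Second, not all of these data are measurements. Kellgren-Lawrence is used as numbered grades in the inclusion criteria, and the Recht criteria classify cartilage degeneration. The label matters because the section has a separate rule for rank data. Calling the grades measurement data takes them outside that rule and makes a t-test and a mean ± SD summary eligible.

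**Working it through.** **The plan's own figure.** The article gives no precision or power figure for the secondary outcomes. Its one computed number is the minimum of 85.49 per group, which concerns the primary effective rate. It reproduces with unpooled variance, two-sided 5% and 90% power (power is inferred, not stated), using the rounded factor 10.5:

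10.5 × (0.956×0.044 + 0.798×0.202) / 0.158² = 10.5 × 0.20326 / 0.024964 = 85.49.

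Nothing below changes it.

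**Step 1: variance.** Let σ² be the between-patient variance, taken as equal at baseline and week 10, and r the correlation between them, taken as equal in both arms. Per patient:

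- week-10 value, unadjusted: σ²
- change score, unadjusted: 2σ²(1−r)
- analysis of covariance on baseline: σ²(1−r²)

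So the covariance analysis has 1−r² of the week-10 variance, and (1−r²)/[2(1−r)] = (1+r)/2 of the change-score variance. The documents give no r, so a range is assumed.

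| Assumed r | Ratio to change score | Ratio to week-10 value |
|---|---|---|
| 0.3 | 0.65 | 0.91 |
| 0.5 | 0.75 | 0.75 |
| 0.7 | 0.85 | 0.51 |
| 0.9 | 0.95 | 0.19 |

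Against change scores, 300 patients with adjustment match 300/0.65 = 462, 300/0.75 = 400, 300/0.85 = 353 and 300/0.95 = 316 patients without it.

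**Step 2: detectable difference.** With 200 against 100, two-sided 5% and 80% power, the smallest detectable difference in SD units is (1.960 + 0.842) × √(1/100 + 1/200) × s = 0.343 × s. Here s is 1, √(2(1−r)) or √(1−r²) for the three analyses.

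| Assumed r | Week-10 value | Change score | Covariance |
|---|---|---|---|
| 0.3 | 0.343 | 0.406 | 0.327 |
| 0.5 | 0.343 | 0.343 | 0.297 |
| 0.7 | 0.343 | 0.266 | 0.245 |

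For a true difference of 0.345 SD, power in the same order is 80%, 66% and 84% at r = 0.3; 80%, 80% and 90% at r = 0.5; 80%, 95% and 98% at r = 0.7.

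**Step 3: which column applies.** The section does not say whether arms are compared on week-10 values or on changes. The descriptions of CSKO and joint space speak of comparison before and after treatment, and the Discussion speaks of changes on X-ray and MRI. That favours the change-score column, without settling it.

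**Step 4: do the named tests go wrong?** Two simulations of 5,000 trials each, at 200 against 100, tested this.

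- On a five-level grade cut from a normal variable, type I error was 5.2% (t) and 5.1% (rank-sum). With a shift of 0.35 SD, power was 77.2% and 76.7%.
- With five equal centres (40 and 20 patients each) and assumed intra-centre correlations of 0.02, 0.05 and 0.10, a t-test ignoring centre had type I error of 4.4%, 4.8% and 3.8%.

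Neither points to an inflated error rate.

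**Step 5: which data are mislabelled.** Joint-space width, thickness and volume are measurements, so the label fits them. The Recht grading and the MRI cartilage-defect score do not fit. The article does not list the Recht levels; I read criteria for degeneration as ordered categories. Kellgren-Lawrence grade is ordered, but no sentence says that arms are compared on it.

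**The case against.** The strongest reply is that nothing here is invalid. In a randomised trial, an unadjusted t-test or rank-sum test is standard and holds its error rate, as step 4 bears out. The primary score is adjusted, so the main conclusion does not depend on this. Adjusting only the primary outcome is a choice, not a contradiction. All of that stands, and it limits the point to efficiency and consistency.

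A reader might infer that the plan uses the wrong test for the grades. The documents do not support that. The rank-sum test is one of the two options for the secondary outcomes and is the stated test for rank data, so a suitable test is already in the plan. The fault is the label, together with the lack of a rule for choosing.

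A reader might also take the 0.51 and 0.19 ratios as the expected gain. They apply only to raw week-10 comparisons, and the wording leans towards change. A change score already removes most stable between-patient variation, so at r = 0.9 little is left to gain.

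It can also be said that covariate models for secondary outcomes belong in a fuller analysis plan. That would answer a silent article. This one names the method, so the method can be judged.

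**Conclusion.** The point holds as a free improvement, confined to the secondary outcomes.

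For CSKO total, medial and lateral joint-space width, cartilage thickness and cartilage volume, the stated tests are valid but less precise than the model already planned for WOMAC. If changes are compared, adjustment removes 5% to 35% of the variance for r between 0.9 and 0.3. If raw week-10 values are compared, it removes 9% to 81% for r between 0.3 and 0.9. The first range is the better guide. Both rest on an assumed r, equal variances at the two times and a common r in both arms. They cover baseline only; no gain from centre has been quantified.

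The measurement label is wrong for the Recht grade and the MRI cartilage-defect score, and for Kellgren-Lawrence grade only if it is compared between arms. It leaves the choice of test open but does not force an unsuitable one. Neither the primary analysis nor the stated sample size is touched.

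**What to change.** Replace the sentence on secondary outcomes with two rules.

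1. **CSKO total, medial and lateral joint-space width, cartilage thickness and cartilage volume:** analysis of covariance of the week-10 value on arm, baseline value and centre, reporting the adjusted difference with its 95% confidence interval. With baseline in the model, the arm difference is the same whether the response is the week-10 value or the change, so this also settles the ambiguity in step 3.
2. **Recht grade or MRI cartilage-defect score, and Kellgren-Lawrence grade if compared between arms:** declare these ordinal. Name one method in advance, either a centre-stratified rank test (van Elteren) or a proportional-odds model with baseline grade and centre. If Kellgren-Lawrence grade is only descriptive, say so.

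The cost is wording. All the values are already collected, and no visit, measurement or sample size changes. The change should be dated and made before the analysts are unblinded.
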